# TUFTS MEDICAL CENTER/TUFTS UNIVERSITY RESEARCH PROTOCOL

**Version date:** 10-Aug-2015

**Principal Investigator:** [name]

**Study Title:** Comparison of soap, hand sanitizer, and 0.05% NaDCC, HTH, and NaOCl chlorine solutions in the development of dermatitis during frequent handwashing

1. Aim and Hypotheses

The aim of this study is to compare the impact of different methods of frequent hand washing used in healthcare settings on the development of irritant hand dermatitis. Subjects will be randomly assigned to one of six different handwashing methods – soap and water, hand sanitizer, 0.05% NaDCC chlorine solution, 0.05% HTH chlorine solution, and both stabilized and unstabilized 0.05% NaOCl chlorine solutions – and will wash their hands ten times daily using their assigned methods for four weeks while researchers monitor skin health and feel daily. We hypothesize that the development of dermatitis on the hands among subjects will vary depending on the substance used for handwashing.

1. **Background and Rationale**
2. **Background**:

Disinfection of hands and surfaces to protect both patients and healthcare providers from disease transmission is a top priority in health care settings worldwide, but frequent handwashing may also cause harm by excessively irritating skin. Health care providers strive to establish protocols that maintain safety from infection and also protect workers from the development of skin conditions such as dermatitis, but these recommendations are inconsistent and lack supporting evidence regarding the impact of washing on skin health. Many commonly used methods of hand washing and disinfection have been implicated in the development of irritant contact dermatitis (ICD)1, a condition of inflammation of the skin characterized by symptoms such as itching, redness, and skin swelling. These uncomfortable and occasionally painful symptoms of ICD are caused by skin barrier disruption, cytokine release, and cellular changes in the skin2. This disruption of the normally protective barrier of the skin can even make sufferers more susceptible to infection by presenting an entry point for disease agents, and especially severe cases may present with clear fissures in the hand that provide an obvious target for infection. ICD is distinct from allergic contact dermatitis (ACD). Although the clinical presentation of the two conditions are similar, ACD is a Type IV delayed hypersensitivity reaction and patients will display a consistent allergic reaction to the substance in question and will patch test positive for that substance3. By contrast, ICD is a non-specific response that may be experienced by a large percentage of a population regularly exposed to irritants commonly associated with dermatitis.

Soap and water, hand sanitizer, and chlorine solutions are all common handwashing solutions that have also been associated with concerns about dermatitis. The use of soap and water or hand sanitizer for handwashing is common in hospitals and clinics, but has been suggested as a common causes of ICD and is widely perceived among healthcare workers as an occupational hazard1. Chlorine solutions are also a common disinfectant used for both surfaces and hands, and due to their powerful disinfecting ability they are particularly widely used in emergency and high-risk scenarios such as the recent outbreak of Ebola Virus Disease (EVD) in West Africa. Chlorine solution can be made multiple ways using different compounds that provide the free chlorine that acts as a disinfectant. These compounds differ in their chemical properties and therefore may differ in the risk they pose to the integrity of the skin barrier on hands. (In Table 1 we provide a summary of the differences in basic properties and common additives among the solutions this study proposes to investigate.) There is some evidence that handwashing with chlorine solutions produced from sodium hypochlorite (NaOCl) and High Test Hypochlorite (HTH) may be linked to ICD4–7, however adequate attention has not been paid to the additives that often exist in these solutions that may act as stronger irritants than the active agents themselves8. For example, unstablized NaOCl has a neutral pH, while the stabilized solution has a much higher pH because of the additions of NaOH. This difference in pH is one factor that might have an impact on dermatitis development. This risk of ICD has not been demonstrated for chlorine solutions made from powdered sodium dichloroisocyanurate (NaDCC). The evidence for the risks associated with all of these handwashing solutions is inconsistent and predominantly observational, making it difficult to disentangle the impact of the handwashing methods themselves from the environments in which they are used.

However this evidence on the impact of these substances on skin relies heavily on observational studies in environments that contain many other irritants1,4,9,10, or on studies of accidental exposure to higher levels of substances than is recommended for handwashing. Studies focused on workers in health care and other occupational settings experiencing irritants within their usual context and are not adequately able to separate the effect of handwashing substances from the environment. Indeed studies have shown that there are numerous factors including weather and baseline reactivity to substances that impact dermatitis1. Other studies focus on the potential for these substances to induce an irritant reactions, but not within a concentration and protocol accepted for handwashing3,5,6. This study will examine the impact of these substances when used appropriately for handwashing in a context where other potential irritants are carefully controlled and tracked to provide high quality evidence on the direct impact of these substances.

|  | **NaDCC** | **HTH** | **NaOCl (Stabilized)** | **NaOCl (Unstabilized)** |
| --- | --- | --- | --- | --- |
| *Original Product Form* | Powder or Tablets | Powder or Tablets | Liquid | Liquid |
| *Chemical Structure* | [figure not shown] | [figure not shown] | [figure not shown] | [figure not shown] |
| *Added Compounds* | 98% Pure (No added compounds) | Compounds to: prevent powdering, prevent absorption of moisture, or help tablet dissolve | Stabilizers (NaOH), Surfactants, Sud suppresors | None |
| *pH* | 6-7 | 10.4 – 10.8 | 10.8-11.4 | ~7 |

*Table 1. Summary of Chlorine Solutions*

Because of this lack of evidence, the recommendations by international agencies and partnerships providing guidelines for safe hand washing and disinfection have been inconsistent and even contradictory. In standard hospital and clinic settings, both the WHO and the CDC recommend handwashing with soap and water or hand sanitizer use, but also acknowledge that frequent use of either method may result in disruption of the normal physiology of the skin barrier on hands11,9. In the context of the recent EVD outbreak in West Africa, international humanitarian organizations have focused on the use of chlorine for handwashing. Doctors Without Borders (MSF) recommends that buckets of 0.05% chlorine solution are prepared using powdered HTH or powdered NaDCC and placed around Ebola Treatment Centers (ETCs) for regular hand washing use12. These recommendations have spilled over into surrounding communities, with 0.05% chlorine solution adopted by government, health, and commercial facilities in West Africa requiring hand washing before entry13. An international organization was recently awarded 5 million euros to install chlorine-based handwashing stations throughout urban and rural areas of Guinea. The WHO recommendation contradicts these suggestions – they advocate hand washing with soap and water or with hand sanitizer containing humectants to prevent skin drying. Hand washing with chlorine, they say, “is not ideal because this may lead to skin lesions, which could increase risk of infection, and because prepared dilutions might be inaccurate.” However they do recommend that if other options are not available or feasible chlorine solution should be available for handwashing14.

Soap and water, hand sanitizer, and chlorine solutions using NaDCC, HTH, and NaOCl are all commonly used in both standard hospital settings and emergency outbreak setting for disinfection of hands to prevent transmission of infection, but the evidence about the risk that these substances may all pose for the development of ICD and subsequent higher risk of infection is inadequate to provide consistent recommendations to healthcare workers and emergency responders. This study will seek to provide clear evidence on this impact of handwashing using these methods by observing the impact of frequent handwashing in a controlled environment.

#### Rationale: There is a lack of evidence about the level of risk different handwashing methods pose for the disruption of the natural skin barrier on hands and development of irritant contact dermatitis. In both traditional healthcare settings and in disease outbreak settings there is a strong need for methods that both provide adequate hand disinfection and protect healthcare workers from the added risk that ICD may pose by disrupting skin’s natural protection. Healthcare workers and the dermatologists who treat occupationally acquired ICD are seeking clearer recommendations for regular handwashing and alternative suggestions for individuals displaying particular sensitivity to commonly used methods, and the international humanitarian community is asking for consistent evidence-based guidance on handwashing in the particularly risky situations where they face highly dangerous infectious diseases such as EVD.

It is difficult to distinguish the causes of dermatitis in these populations, since healthcare workers and all those who wash hands regularly are commonly exposed to a range of substances acting as irritants that may cause dermatitis1. Therefore there is a need to study the impact of these handwashing methods while controlling for other substances that may cause a skin reaction. The results of this study will provide evidence-based recommendations aligning contradictory guidance to healthcare workers in settings across the globe, and are particularly relevant to international organizations concerned with the most recent EVD outbreak. The outbreak in West Africa is the largest to date, establishing the potential for large and devastating outbreaks with reproductive rates >115. Clear handwashing protocols are an essential practical recommendation to prevent future outbreaks attaining the size and duration of the most recent outbreak devastating West Africa.

1. **Research Plan**

### Experimental design:

### This study consists of an individually randomized controlled trial with six arms to assess the impact of six different methods of frequent handwashing (soap and water, hand sanitizer, 0.05% chlorine solution made with NaDCC, 0.05% chlorine solution made with HTH, 0.05% stabilized chlorine solution made with NaOCl, 0.05% unstabilized chlorine solution made with NaOCl) on development of dermatitis.

*Recruitment and Enrollment*: Subjects will be recruited using flyers posted around the Medford/Somerville area and newspaper advertisements taken out in the Tufts Daily, the Somerville Journal and the Medford Journal (Appendix A). These advertisements will describe the purpose and requirements of the study and provide contact information for the study team. The flyer will also be distributed as an image to public listservs and social media groups such as the Medford Moms email list and Tufts campus email lists. Individuals who feel that they meet the study’s criteria may attend one of several 1 hour meetings during which researchers will explain the study in detail (Frequently Asked Questions in Appendix B). Potential volunteers will be given the opportunity to ask questions about the study in a group setting. After the meeting subjects will meet with researchers individually to ask further questions they may be uncomfortable asking in a public setting and study staff will collect written informed consent (Appendix C) in a private setting. Subjects who consent to the study will then be asked to schedule a time to complete the baseline survey and data collection. Potential volunteers who do not wish to attend a group meeting or are unable to attend at the posted time may schedule a meeting with researchers to learn about the study individually and provide informed consent if they choose to participate.

*Baseline Assessment and Exclusion Criteria*: At baseline, subjects will 1) respond to a questionnaire (Appendix D), 2) have to a hand exam (Appendix E) and 3) have a patch test applied to test for allergy to any of the study substances (Appendix F). This baseline data will also be used to confirm that subjects do not meet any of the study’s exclusion criteria. The questionnaire will include demographic and contact information, information about personal history of dermatitis and atopic disposition (history of seasonal allergies, asthma, childhood eczema, and hay fever), and typical handwashing behavior. The hand exam will look for signs of current dermatitis or baseline skin abnormalities and assess a score from 0-360 using the Hand Eczema Severity Index (HECSI)16. The patch testing kit (8mm Finn Chambers® on Scanpor® Tape) will be applied using dilutions of all six substances included in the study (soap, hand sanitizer, NaDCC, HTH, stabilized NaOCl, unstabilized NaOCl) in two locations - on the upper back to comply with the gold standard of testing and on the arm to allow for ease of viewing and reporting by subjects.

Subjects will be instructed on how to remove the patches and mark the area tested with a surgical marker 48 hours after application. Subjects will take photos of the patch site and provide the photos to researchers via email, and will also be instructed to notify the study team if they observe any redness inside the target areas. Subjects will also be given the option to report in person to have a photo of the area taken if they are unable to take a photo or uncomfortable emailing the photo to researchers. Subjects will repeat the observation and provide another photo on the 96-hour mark. On Day 7 after application subjects will be seen in person by research staff, who will verify negative patch testing and refer any suspected positive cases to [name], co-PI on the study, for verification.

Subjects who are pregnant or trying to become pregnant and those with a history of dermatitis, any baseline skin abnormalities upon exam, a positive patch test to any study substance, or who are employed in a profession in which hands are regularly exposed to irritants (e.g. healthcare workers, mechanics, hairdressers/cosmetologists, bartenders or dishwashers) and those with a self-reported history of mental health issues that may be triggered by a study related to hygiene will be excluded from the study.

*Randomization*: Subjects will be randomized into one of the six treatment groups using a computer-generated randomization list prepared by a researcher not involved in the running of the trial.

[figure not shown]

*Fig 1. Treatment Groups*

*Intervention*: At the beginning of the intervention subjects will be given a drawstring bag containing handwashing materials and hypoallergenic hygiene items including shampoo, conditioner, soap, and fragrance-free Vaseline along with instructions for use (Appendix G). Subjects will be asked to use the provided hygiene items in lieu of their usual products in order to control for possible other causes of skin irritation for the duration of the experiment. Subjects will be told that they can moisturize using the Vaseline as much as they would like. Vaseline is the best choice for this purpose because it is hypoallergenic, consistent with the way that healthcare workers commonly manage any skin itchiness and dryness, and consistent with available options for moisturizing in both the United States and West Africa. During the four weeks of intervention, subjects will be asked to wash their hands 10 times daily with the substance assigned to their treatment group, and instructed to use the soap provided in the hygiene kit for any hand or body washing they may do above and beyond the handwashing with their assigned substance (instructions in Appendix H). Each evening subjects will be asked to report to Anderson Hall on the Tufts Medford campus to pick up a refill of their assigned handwashing materials. Refills of the hygiene items will be available as needed. During the pickup time each day, subjects will also answer a brief questionnaire administered on tablets assessing adherence to the handwashing protocol, self-assessment of hand feel (including itchiness, pain, redness, flaking, cracks, skin thickening or swelling), receive a brief physical hand examination from study personnel, and take photos of both sides of each hand (Appendix I). The photos and hand exam scores will be reviewed daily for signs of dermatitis or skin abnormalities, and any suspected cases will be referred to [name] for treatment and assessment to determine whether continuation in the study is recommended. Dermatitis will be assessed using the HECSI scale, and the severity of the score will be used to guide the most likely course of action as described in Table 2 below.

*Endline*: Endline data collection will occur on the last day of the intervention. All subjects will respond to the daily questionnaire and receive a hand exam as usual, and patch testing will be applied a second time according to the same protocol used during baseline. As during the previous assessment, subjects will remove the patch, mark the area, and take pictures after 48 and 96 hours and the area will be examined in person by a researcher on Day 7. Any suspected positive cases will be referred to [name] for verification and subjects with a confirmed positive will be recommended to avoid the substance in the future.

*Data Analysis*: As a preliminary study, the analysis for this study will be descriptive and foundational for further studies examining substances that show promise. The primary outcome of this study is the development of dermatitis, as measured by both HECSI score and self-perception index where subjects are asked to describe symptoms and discomfort experienced on a scale from 1-10. The HECSI score is a highly sensitive tool designed for use in research and epidemiological studies, and will serve as the gold standard of measurement for clinical dermatitis. However perception and discomfort are highly important aspects of the impact of dermatitis on patients, meaning the self-perception index adds an important dimension to the measurement of dermatitis as an outcome. We plan to compare the proportion of subjects presenting with signs and symptoms of dermatitis in each treatment group, and to stratify the results by gender and history of atopy in order to control for potential confounders.

[figure not shown]

*Figure 2. Study Timeline*

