### Sample size and statistical analysis(es) :

### We plan to enroll 108 total subjects in the study, with 18 randomized to each arm. We will target this number with the understanding that minor attrition may occur, and estimate that we need 15 subjects per arm to complete the study to achieve our goals.

**Randomization Methods**: Randomization will be done after patch-testing results are read, to ensure that no subjects meeting exclusion criteria are involved in the study intervention. A researcher who does not interact directly with subjects will perform randomization. Subjects will be numbered (1-108). 18 subjects will be assigned to each group. A random number generated will be used to generate 18 numbers between 1 and 108. These subjects will be assigned to the first intervention group. Random number generation will be repeated in this way five times, with subjects corresponding to the number assigned to the treatment group for the round. The 18 remaining subjects will be assigned to the last treatment group.

**Blinding**: Researchers assessing HECSI scores for the hand exam and applying and interpreting results of the patch testing will be blinded to subject treatment group. Daily surveys will not record treatment arm and subjects will be instructed not to identify their group to examiners.

It is not possible to blind subjects to treatment, because the difference between soap and water, hand sanitizer, and chlorine solutions are obvious and cannot be obscured. However subjects assigned to one of the chlorine solution treatment groups will not be told which solution they have been assigned.

**Sample Size Calculations:** Because there are no previous handwashing studies using chlorine, soap, or hand sanitizer for handwashing that can provide information on the number of subjects likely to develop dermatitis we are unable to calculate a meaningful sample size for statistical significance. We feel that this small sample size is appropriate for a first study. For example if 20-100% of participants in a given arm develop dermatitis that will suggest that the method is problematic and should not be recommended, but if 0% of participants develop dermatitis this will be good evidence that the method has potential and should be studied further. This study is intended to be a first investigation that can provide information that could be used in the future for sample size calculations for a larger trial if any of the handwashing materials show potential.

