### Laboratory tests: None

### Study Procedures:

### *Hand exam*: Subjects will receive a visual inspection of hands assessing a score for the severity of erythema, infiltration/papulation, vesicles, fissures, scaling, and edema at different locations on the hands and the extent of the area affected. This evaluation is used to calculate a HECSI score at baseline, and daily during the intervention using the form in Appendix E. Photos of hands will also be taken daily.

*Patch Testing*: Subjects will have patch testing done at baseline and endline for all the substances included in the study with data and results recorded in the form shown in Appendix F. Each substance used in the study will be diluted and placed on the skin under a patch sealed with hypoallergenic tape (8mm Finn Chambers® on Scanpor® Tape) in two areas – on the back and upper arm. Testing on the back provides the gold standard, and patches on the arm will allow for easy observation and reporting by subjects. 48 hours after application, subjects will be asked to remove the patch, identify the testing area by marking it with a surgical marker, and take a photo of the area to provide to researchers. Subjects will provide another photo 96 hours after application. Subjects will be instructed to contact study staff if they observe any redness or suspect a reaction within one of the six testing areas. 7 days after testing, researchers will visually inspect the patch-testing site. Suspected positives will be referred to [name] for confirmation.

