Contact information including phone number and email address will be collected for each patient, and patients will be notified of any changes in the study in writing either through email or in person. These written records of changes will be archived and a description of changes included in any write up of study methods.

1. **Payment, including a prorated plan for payment**: Subjects will receive a total of $600 after successful completion of all study activities. Subjects will receive $100 for each round of patch testing is completed, and $100 for each week of the intervention completed. Although this study presents minimal risk to subjects, a high level of compensation is called for due to the study’s labor-intensive nature including consistent attention to details and the high level of compliance to intervention activities and attendance at assessments over the course of 7 weeks and the inconvenience of patch testing procedures. The fees will be paid in three stages: $100 after the baseline assessment, $200 at the midpoint of the intervention, and $300 after the endline assessment.
2. **Payment for a research-related injury**: [name] will examine any subjects showing signs of dermatitis. Over the counter treatment will be provided by the research team if necessary, but subjects will be covered by personal medical insurance for consultations at [name] clinic. If subjects do not have sufficient insurance the study will cover the costs of this consultation. Subjects will be reimbursed up to $100 for transportation to a consultation at [name] office. Subjects will not be financially compensated for any research-related injuries.
3. **Outcome**: We expect low levels of our primary outcome of dermatitis (as measured by visual dermatitis scale assessed by study staff) and secondary outcome of discomfort (as measured by self-perception of hand feel) and any level of dermatitis, including 0%, will provide valuable data. However a high level of compliance is necessary for the success of the study and will be measured by self-report and observation of materials. We define high compliance as >95% completion of study intervention activities, as measured by survey completion, pickup of materials, and self reported handwashing 10x per day.

1. **Tissue banking considerations**: None

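### Self-perception is part of the primary outcome in the Data Analysis paragraph but a secondary outcome in the Outcome item; the two cannot both be followed

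*Protocol*

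**What the plan says.** The Data Analysis paragraph (Research Plan, Experimental design) states: "The primary outcome of this study is the development of dermatitis, as measured by both HECSI score and self-perception index". The index is a 1-10 rating by the subject. The same paragraph says that HECSI "will serve as the gold standard of measurement for clinical dermatitis", and that the index adds a further dimension because discomfort matters to patients. It then sets out the comparison: "We plan to compare the proportion of subjects presenting with signs and symptoms of dermatitis in each treatment group".

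The Outcome item under Subject Participation ranks the measures differently: "primary outcome of dermatitis (as measured by visual dermatitis scale assessed by study staff) and secondary outcome of discomfort", the latter being how subjects say their hands feel. It does not name HECSI. The Hand exam paragraph under Study Procedures supplies the link, since the staff's visual inspection is what produces the score: "This evaluation is used to calculate a HECSI score at baseline, and daily during the intervention using the form in Appendix E". The Intervention paragraph also says that dermatitis is assessed on HECSI, and the protocol describes no other staff-scored dermatitis scale.

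On masking, the Blinding paragraph says: "It is not possible to blind subjects to treatment". It adds that HECSI examiners are blinded and that subjects in the four chlorine arms are not told which chlorine solution they have.

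The Sample Size Calculations paragraph illustrates how an arm might be read: 20-100% developing dermatitis would suggest a problem, and 0% would suggest promise.

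**The concern.** One instrument is primary in one place and secondary in another. A statistical analysis plan can add thresholds and table layouts, but it cannot agree with both statements. Whoever writes up the trial could headline either version and cite the protocol for it.

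The conflict matters more because the two measures differ in their protection against bias. HECSI is scored by blinded examiners. The index is completed by subjects who know whether they use soap, sanitizer or chlorine, and who may hold views about chlorine on skin. If self-report enters the primary proportion, part of a difference between arms could reflect those views. The phrase about signs and symptoms makes this possible without saying how the two would be put together.

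**Working it through.** **1. The two statements side by side.**

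| | Data Analysis paragraph | Outcome item |
|---|---|---|
| Staff-scored hand exam (HECSI) | Primary | Primary |
| Self-perception | Primary, jointly | Secondary |
| Quantity compared | Proportion with signs and symptoms | Not stated |

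They agree on HECSI and disagree on self-perception. Neither stands in an amendment log.

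**2. The plan's own figures.** 6 arms × 18 = 108, as stated; 6 × 15 = 90 completers. No alpha, power or effect size is given, and the protocol says that it could not calculate a meaningful sample size. There is therefore no power figure to reproduce or overturn.

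**3. How many comparisons involve known product types.** Six arms give 6 × 5 / 2 = 15 pairs. The four chlorine arms give 4 × 3 / 2 = 6 pairs among themselves. The other 15 − 6 = 9 involve soap or sanitizer, where subjects know the type of product.

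**4. How far the case definition can move the proportion.** The documents give no rates, so these are assumptions. Let h be the share of HECSI cases and s the share of self-report cases overall, with or without HECSI findings.

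- HECSI alone: h.
- Case on *either* measure: max(h, s) with full overlap; h + s − hs with independence.
- Case on *both* measures: min(h, s) with full overlap; hs with independence.

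With h = 5% and s = 20%:

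- HECSI alone: 5%.
- *Either*: 20% (full overlap) to 0.05 + 0.20 − 0.01 = 24% (independence).
- *Both*: 5% (full overlap) to 0.05 × 0.20 = 1% (independence).

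Other assumed pairs show the range, again from full overlap to independence:

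| h, s | HECSI alone | *Either* | *Both* |
|---|---|---|---|
| 5%, 20% | 5% | 20% to 24% | 5% to 1% |
| 10%, 30% | 10% | 30% to 37% | 10% to 3% |
| 20%, 40% | 20% | 40% to 52% | 20% to 8% |

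**5. In subjects.** With the 15 completers per arm that the protocol asks for, 20% is 0.20 × 15 = 3 cases. At 5% and 20%, the expected cases per arm are:

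- HECSI alone: 0.05 × 15 = 0.75.
- *Either*: 3.0 to 3.6.
- *Both*: 0.75 to 0.15.

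The chance that an arm shows no case, (1 − p)^15, is:

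- HECSI alone: 0.95^15 = 46%.
- *Either*: 0.80^15 = 3.5% to 0.76^15 = 1.6%.
- *Both*: 0.95^15 = 46% to 0.99^15 = 86%.

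The same subjects can therefore look free of dermatitis or near the 20% guide value, depending on the definition.

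**The case against.** The strongest reply is that the Data Analysis paragraph never forms a composite. It calls HECSI the reference standard and the index an added dimension, which reads naturally as two measures reported side by side. The Intervention paragraph ties dermatitis to HECSI. The analysis is declared descriptive, both measures are collected daily, and both can be shown in full whichever is called primary. Most of this stands, and it limits the consequence. It does not remove the conflict: side-by-side reporting as joint primary outcomes still disagrees with the Outcome item.

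Several stronger readings are tempting, and the documents do not support them.

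- *The primary outcome is an either-or composite.* The text allows this but does not state it. The *either* and *both* results above show what is left open, not what is planned.
- *20% is a decision rule.* It is introduced as an example, in a paragraph explaining why no sample size was calculated, and it refers to developing dermatitis. If that means HECSI, symptom reports alone would not move an arm across it. In the 5% and 20% illustration, moreover, the assumed self-report rate equals the guide value, so reaching it under *either* is built in.
- *Independence is the expected case.* It is unlikely. Subjects rate redness, flaking, cracks and swelling, which overlap the erythema, scaling, fissures and edema scored by the examiner. That is why full overlap is given as the other end of each range.
- *Unblinded subjects are an error.* The protocol discloses this and gives the reason. It matters here only because self-report may enter the primary result.
- *Comparisons among the chlorine arms are unbiased.* Subjects are not told their solution, but nothing says that the solutions are indistinguishable, and Table 1 lists differences in pH and additives. This is partial masking.
- *The index lacks a pre-exposure value.* The baseline questionnaire is in Appendix D, which is not shown, so this cannot be judged and no extra questionnaire is called for.

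**Conclusion.** The protocol contradicts itself on whether self-perception belongs to the primary outcome, and the passages must be reconciled. Reading the Outcome item as HECSI is an inference, but a sound one from the Intervention and Hand exam paragraphs.

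The consequence is confined to which result is headlined as primary and what counts as a case. No error rate, power or sample-size figure is affected. Within that limit the effect can be large relative to the protocol's own guide values of 0% and 20%: with the assumed rates of 5% and 20%, the proportion per arm runs from 1% to 24% across the possible definitions, against 5% for HECSI alone. These rates are illustrative, and the size of the effect depends on them and on the overlap between the measures. The contradiction does not.

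**What to change.** Amend the Data Analysis paragraph to agree with the Outcome item:

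- One primary outcome: dermatitis by HECSI, scored by the blinded examiner.
- The proportion compared between arms is defined on HECSI, in place of the phrase about signs and symptoms.
- The self-perception index is a separate secondary outcome. Comparisons involving soap or sanitizer are labelled as subject-unblinded. Comparisons among the chlorine arms are described as partially masked, with subjects not told which solution they have, and not as unbiased.
- Name HECSI in the Outcome item, so that the two places use the same term.

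This follows the protocol's own description of HECSI as its reference measure and keeps the self-report in view. The cost is a few sentences of protocol wording, with no new visit, form or measurement and no change to enrolment.
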